Despite the benefits aforementioned, the intradialytic exercise program is not commonly incorporated into regular HD care worldwide. After all, the formal recommendation from the ACSM is to perform exercise training for a minimum of two hours after, but not during, HD [10]. In Taiwan, no HD unit incorporates an exercise program as part of regular care. Very few studies have evaluated the effects of structured intradialytic exercise programs on the level of physical activity and HRQoL of HD patients [13,14,15]. According to the ACSM’s guideline for an exercise prescription [10], the frequency of aerobic exercise for HD patients is 3 to 5 days per week. Whether a low frequency of exercise (such as two days per week) produces similar therapeutic effects is unclear. The objective of this randomized control trial is, therefore, to compare the efficacy of different frequencies of structured intradialytic exercise programs on Asian HD patients in Taiwan.

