### 2.5. Statistical Analysis and Power Estimates

Statistical analyses will be performed using SPSS, version 22.0 (SPSS Inc., Chicago, IL, USA). The Shapiro–Wilk test of normality will be used to evaluate the distribution of each outcome variable. If data are normally distributed, paired t*tests and analysis of variance (ANOVA) will be used. If data are not normally distributed, the Wilcoxon signed-rank test and Kruskal–Wallis test will be used. The preintervention outcome measures will be compared using ANOVA or Kruskal–Wallis test. Paired t-tests or Wilcoxon signed-rank test will be applied to compare differences between pre- and post-tests. After the exercise intervention, intergroup comparisons regarding improvements of outcome measures will be determined using ANOVA or Kruskal–Wallis test.

The G*Power (Germany, version 3.1.9) software will be used for sample size estimation [22]. Based on repeated measures ANOVA, a statistical power of 0.8, a significant level of 0.05, the effect size is 0.35, refs. [23,24,25], and a minimum of 84 participants are required for our study. We noted the likelihood of a high drop-out rate for intradialytic exercise [26].

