## 3. Discussion

Despite good evidence on the benefit of exercise training on physical function, and that such training could reduce a sedentary lifestyle among HD patients, the benefits related to different frequencies of intradialytic exercise protocols in Asian populations is largely unclear. While an intervention with intradialytic exercise is generally considered safe among diverse racial and cultural populations, the best frequency of interventions remains to be investigated.

HD is associated with a high prevalence of psychological problems [27]. Among the HD population, depression is the most common mental disorder. Furthermore, the prevalence of depression in these patients is higher than those in other chronic disease populations [27]. A previous study reported that, based on the mental component scale of SF-36, Taiwanese HD participants had scores significantly lower than the general population [28]. While a recent systematic review advocated that regular exercise may reduce depression and fatigue in HD patients [29], results are still inconsistent across studies [30,31,32]. Hence, our study aims to provide useful information bridging the knowledge gap in Asian populations.

Current evidence supports that moderate-intensity exercise training effectively improves HRQoL [33]. In addition, two systematic reviews and meta-analyses showed that intradialytic exercise is associated with better HRQoL [23,31]. However, another two studies reported no significant difference in HRQoL after intradialytic exercise [29,34]. Regarding the mode of intradialytic exercise, Gomes et al. reported that aerobic exercise alone is not significantly associated with HRQL [32]. In our proposed study on patients under HD, we will incorporate resistance training for knee extensors after the aerobic cycling exercise. Together, they will likely constitute a more comprehensive exercise program.

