Most intradialytic exercises in the literature, including the best-known CYCLE-HD study, were conducted for 30 min and given three times a week [11,13,14,15,16]. There is only one study that used the exercise frequency of two times a week, and the training mode involved resistance training and stretching, but not aerobic training [44]. Some other studies also adopted the exercise frequency of two to three times a week, such as those of Vilstreren et al., Chigira et al., and Bae et al. [45,46,47]. To our knowledge, no study has yet directly compared intradialytic exercise groups specifically between three times and two times a week. Since cycle ergometer devices and healthcare givers monitoring intradialytic exercise may be limited in some hospitals in different countries, whether the frequency of intradialytic exercise could be reduced is a crucial and practical issue that needs to be clarified. Hence, we have designed this comparative study in order to clarify this issue and try to fill the knowledge gap in the field of intradialytic exercise.

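### The 0.8 power behind the 84 participants is power for a three-arm omnibus test; it does not apply to the comparison of three with two sessions a week

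*Protocol article*

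**What the plan says.** The Introduction gives the objective as "to compare the efficacy of different frequencies of structured intradialytic exercise programs on Asian HD patients in Taiwan". The Conclusions expect the results to show whether the lower frequency does about as well. The arms are three sessions a week, two sessions a week, and usual care (section 2.2.2).

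Section 2.5 sizes the trial with G*Power on a repeated measures ANOVA, with "a statistical power of 0.8", "a significant level of 0.05", and an effect size and total given as "a significant level of 0.05, the effect size is 0.35, refs. [23,24,25], and a minimum of 84 participants are required for our study". It names no metric for 0.35, no outcome scale and no pair of arms. The planned between-group test is a three-group ANOVA or Kruskal–Wallis test on improvement.

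Of the three references behind 0.35, only number 23 is described in the text. The Discussion says that "two systematic reviews and meta-analyses showed that intradialytic exercise is associated with better HRQoL [23,31]". The Discussion also says, to the authors' knowledge, that "no study has yet directly compared intradialytic exercise groups specifically between three times and two times a week".

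**The concern.** The only power figure in the article is attached to the study as a whole, and the study is presented as a frequency comparison. A reader will naturally take 0.8 as the chance of detecting a difference between three and two sessions. Neither the source of the effect size nor the planned test supports that. The one described source concerns whether intradialytic exercise helps, and a three-arm test answers whether any arm differs from any other.

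The risk lies in reading the results. If three and two sessions do not differ significantly, and the trial is believed to have had 80% power for that contrast, the result could be taken as good evidence that two sessions suffice. The Discussion treats that as a practical question for units with few ergometers and staff, so a mistaken reading would have consequences.

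**Working it through.** **Inputs.** From section 2.5: effect size 0.35, alpha 0.05, power 0.8, N = 84. From section 2.2.2: three arms. Assumptions, because the article does not give them: 0.35 is Cohen's f (the usual G*Power input for ANOVA), 1:1:1 allocation (84/3 = 28 per arm), a single-measure analysis, two-sided pairwise tests, no drop-out, and no multiplicity adjustment.

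**1. Reproducing 84.** For a one-way ANOVA the noncentrality is λ = f²N, with 2 and N − 3 degrees of freedom.
- N = 84: λ = 0.1225 × 84 = 10.29; power 0.812.
- N = 81: λ = 0.1225 × 81 = 9.92; power 0.796.

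So 84 is the smallest equal-arm total that reaches 0.8 for the test of any difference among three arms. Repeated-measures settings with three measurements and a correlation of 0.5 give 57 (between-group factor) or 21 (group-by-time interaction) instead. A two-measurement interaction under G*Power's Cohen option also gives 84, and that too is a three-arm omnibus test.

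**2. What f = 0.35 implies for three against two sessions.** Set usual care at 0, three sessions at k, and two sessions at p·k, where p is the share of the three-session benefit that two sessions retain. Choose k so that the SD of the three arm means is 0.35 in units of the outcome SD. Then:
- difference between three and two sessions = k(1 − p), with standard error √(2/28) = 0.267;
- pooled exercise minus usual care = k(1 + p)/2, with standard error √(1/56 + 1/28) = 0.231;
- power from the noncentral t distribution with 81 degrees of freedom.

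| Share p | k (SD) | 3x − 2x (SD) | Power, 3x v 2x | Power, pooled exercise v usual care |
|---|---|---|---|---|
| 1 | 0.74 | 0 | 0.05 | 0.89 |
| 0.8 | 0.81 | 0.16 | 0.09 | 0.88 |
| 2/3 | 0.84 | 0.28 | 0.18 | 0.85 |
| 1/2 | 0.86 | 0.43 | 0.35 | 0.78 |
| 1/4 | 0.82 | 0.62 | 0.63 | 0.59 |
| 0 | 0.74 | 0.74 | 0.78 | 0.35 |

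The omnibus power is 0.81 in every row, because f is fixed. Power for three against two sessions is highest at p = 0, and even there it is 0.78.

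**3. Detectable difference and precision.** With 28 per arm, 80% power for three against two sessions needs a difference of about 0.76 SD. That slightly exceeds the whole gap between exercise and usual care when both exercise arms do equally well (0.74 SD). The 95% confidence interval half-width is 1.990 × 0.267 = 0.53 SD, and wider with drop-out.

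**The case against.** **The protocol never claims pairwise power.** This is true. Section 2.5 ties 0.8 to an ANOVA, and a condensed article may leave the list of contrasts to the full plan. What stands against it is that the article itself publishes a power and a sample size for a study whose declared purpose is the frequency comparison, and its only between-group test does not isolate that comparison. The point is about what the stated figure covers, not about a missing list of contrasts.

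**The source of 0.35 is not fully known.** A reader might infer that 0.35 cannot be a frequency effect and must be an effect of exercise against no exercise. The documents do not support that. References 24 and 25 are not described, the statement that no direct comparison exists is limited to the authors' knowledge, and 0.35 may simply be an assumed value. All that can be said is that the text shows no frequency-specific basis for it.

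**The 0.8 might be thought to belong to exercise against usual care.** This too goes further than the figures allow. Power for the pooled contrast is 0.78 to 0.89 when two sessions keep at least half the benefit, but 0.35 when they keep none. Nor must the two exercise arms differ by less than exercise differs from usual care: the Introduction calls the effect of two days a week unclear, and at p = 0 the two gaps are equal.

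**The figures are conditional.** They assume equal arms, one measure per patient and no drop-out, while section 2.5 names repeated measures and expects high drop-out. That limits their precision, so they should be stated with these conditions. Drop-out would only lower the power.

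**Conclusion.** The point holds in a limited form. On the reading that reproduces 84, the stated 0.8 is the power of a three-arm omnibus test at f = 0.35. With the same f and 28 per arm, power for three against two sessions is 0.05 to 0.35 if two sessions keep at least half the three-session benefit, and at most 0.78 if they keep none. The stated 0.8 is therefore not reached for the frequency comparison anywhere in that range.

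This rests on reading 0.35 as Cohen's f, equal allocation, a single-measure analysis, no drop-out, and a two-session effect between usual care and three sessions. An ordering with usual care midway between the two exercise arms would give a difference of 0.86 SD and power of 0.88, but nothing in the protocol suggests it. The sample size is not arithmetically wrong. The fault is that its power is given for the study without saying that it does not cover the study's main question.

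**What to change.** Keep N = 84 and amend section 2.5 as follows.

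- State that 0.8 is the power of the three-arm omnibus test at f = 0.35, and that three against two sessions is not separately powered.
- State that, under 1:1:1 allocation, a single-measure analysis and no drop-out, the difference between three and two sessions detectable with 80% power is about 0.76 SD.
- Pre-specify the three-minus-two-sessions contrast, reported as an estimate with its 95% confidence interval (half-width about 0.53 SD, wider with drop-out).
- State that a non-significant result on this contrast will not be read as showing similar effects.

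Do not write that 0.35 is an effect of exercise against no exercise, or that 0.8 applies to pooled exercise against usual care. The pooled contrast may be added, provided the text says that its power depends on the pattern of arm means.

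The cost is a few sentences and one pre-specified contrast, with no extra patients, visits or data. The downside is a less favourable stated power for the frequency question.

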### 2.6. Safety

The criteria for immediate interruption of the exercise includes intense physical exhaustion, chest pain, dyspnea, dizziness, unstable heartbeat and blood pressure, cramping, or fatigue of the lower limbs. For each participant, serious adverse events and reasons for withdrawal from this study will be recorded accordingly.

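### The plan expects high drop-out from intradialytic exercise, which only two of three arms receive, yet fixes change-score tests that drop every patient without the follow-up value

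*Protocol article*

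**What the plan says.** - **Expected loss.** Section 2.5 closes the sample-size paragraph with "We noted the likelihood of a high drop-out rate for intradialytic exercise". It gives no rate, no split by arm and no consequence for the design.
- **Who can be affected.** Section 2.2.2 randomises to exercise three times a week, exercise twice a week, or usual care. Usual-care patients have no programme to give up.
- **Analysis.** Section 2.5 states that "intergroup comparisons regarding improvements of outcome measures will be determined using ANOVA" or the Kruskal-Wallis test, with paired t or Wilcoxon signed-rank tests for change within an arm.
- **Follow-up.** The Abstract follows subjects for 24 weeks, with SF-36 at 0, 12 and 24 weeks. Section 2.1 sets three measurement points without linking them to continued exercise.
- **Stopping and leaving.** Section 2.6 lists criteria for interrupting exercise and separately says that "serious adverse events and reasons for withdrawal from this study will be recorded accordingly". It does not say what assessments a patient has after giving up the programme.
- **Sample size.** Section 2.5: "Based on repeated measures ANOVA", "a statistical power of 0.8", "a significant level of 0.05", "the effect size is 0.35", and "a minimum of 84 participants are required for our study".

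**The concern.** The section names a threat and then commits to tests that are exposed to it. A change score needs both a baseline and a follow-up value. A patient with no later SF-36 is absent from every comparison, and one seen at week 12 but not at week 24 contributes nothing to the week-24 comparison.

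If loss is heavier in the exercise arms and falls on patients who are doing worse, the analysis compares patients who tolerated the programme with nearly all usual-care patients. If loss also differs between three and two sessions a week, it distorts the frequency comparison on which section 4 wants to conclude. Part of the burden of the higher frequency would then be removed from the data.

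An analysis plan can define an analysis set later, but it cannot recover questionnaires that were never collected. Whether SF-36 continues after exercise stops therefore has to be settled in the protocol.

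**Working it through.** **1. The plan's own figure.** Inputs from section 2.5: alpha 0.05, power 0.80, effect size 0.35 (read as Cohen's f; the metric is not named), three arms. A one-way ANOVA with noncentrality λ = N × f² gives:
- N = 81: λ = 81 × 0.1225 = 9.92, power 0.796
- N = 84: λ = 84 × 0.1225 = 10.29, power 0.812

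So 84 is reproduced as a one-way three-group ANOVA with no allowance for loss. (Repeated-measures variants with three measurements and correlation 0.5 give 57 for between-arm, 15 for within-patient and 21 for interaction effects.) If 84 are randomised and 20% or 40% have no follow-up value, 67 or 50 remain, and power is 0.71 or 0.56.

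**2. Planned effect in SD units.** If both exercise arms differ from usual care by d, then f = d√2/3. Hence d = 0.35 × 3/√2 = 0.742 SD.

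**3. Bias of the completer comparison.** Let a share p leave an arm, and let leavers do worse on SF-36 change than stayers by g SD. The completer mean then exceeds the all-randomised mean by p × g. Between exercise and usual care the bias is g × (p_ex − p_uc). The article gives neither p nor g, so both are assumptions.

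| Loss, exercise / usual care | g = 0.3 | g = 0.5 | g = 0.8 |
|---|---|---|---|
| 20% / 5% | 0.045 | 0.075 | 0.12 |
| 30% / 10% | 0.06 | 0.10 | 0.16 |
| 40% / 10% | 0.09 | 0.15 | 0.24 |

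The range is 0.045 to 0.24 SD, or 0.045/0.742 = 6% to 0.24/0.742 = 32% of the planned effect. Pairing the same limits differently gives 0.3 × (0.20 − 0.10) = 0.03 SD to 0.8 × (0.40 − 0.05) = 0.28 SD. With equal loss and the same g in every arm, the bias is g × 0 = 0.

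**4. Type I error.** Simulation: 20,000 trials, 28 per arm (84/3, assuming equal allocation), all-randomised means equal, ANOVA on completers.

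| Loss in the three arms (usual care last) | g = 0.5 | g = 0.8 |
|---|---|---|
| 30 / 30 / 10% | 6.0% | 7.7% |
| 40 / 30 / 10% | 6.9% | 9.4% |

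At g = 0.3 the rate is about 5.4%, barely above nominal. A harsher model confines loss to the exercise arms, with correlation 0.4 between staying and change. It gives 0.14, 0.20 and 0.26 SD bias at 20%, 30% and 40% loss, and type I error of about 7%, 9% and 13%.

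**5. Would using week 12 help?** Suppose the 30% with the lowest week-12 change in one arm are lost afterwards, and week-12 and week-24 change correlate 0.4 (assumption). The week-24 completer mean is too high by 0.4 × φ(z₀.₃)/0.7 = 0.4 × 0.348/0.7 = 0.20 SD. An estimate that also uses the week-12 values of those lost is close to unbiased, because the loss depends on data that were observed. A patient lost before week 12 has no such value and cannot be recovered by the model.

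**The case against.** The strongest objection is that the article is silent rather than wrong. Analysis sets and missing-data handling are commonly left to the analysis plan, and a test on change is compatible with analysis as randomised. This stands as far as it goes, and the absence of an intention-to-treat statement is not the point here. The point is that a foreseen, intervention-linked loss sits beside named tests that discard incomplete patients.

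Three stronger readings are tempting, and the article supports none of them:
- *Stopping exercise counts as leaving the trial.* The drop-out sentence is ambiguous. Section 2.6 mentions interruption and withdrawal separately, and the Abstract follows all subjects for 24 weeks.
- *Only patients who improve are compared.* Improvement in section 2.5 means change in the outcome. Patients who stay the same or worsen remain in.
- *The exercise arms will look better than they are.* That needs loss that is both unequal and related to outcome. The article documents neither.

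It is also fair that a mixed model adds nothing for a patient with no value after baseline, and that it assumes data missing at random. For such patients only continued collection helps. The model's gain is confined to those seen at week 12 but not at week 24.

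**Conclusion.** The concern holds in a conditional form. Section 2.5 expects high drop-out from an intervention given to two of three arms, and fixes tests that, as written, lose every patient without the follow-up value and waste week-12 data when week 24 is missing. Whether SF-36 is collected after exercise stops is left open.

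If loss is heavier in the exercise arms and goes with poorer SF-36 change, the result may favour exercise by about 0.05-0.24 SD, with type I error of about 6-10% at the larger gaps. These sizes rest wholly on the assumed losses (20-40% against 5-10%) and gap (0.3-0.8 SD). At the low end the effect is small, and under equal loss related to outcome in the same way it is nil. A bias in this trial is therefore possible but not shown. The change is worth making because it is cheap and cannot be made after the data have been missed.

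**What to change.** In section 2.5:
- Replace the ANOVA on change by a mixed model for repeated measures of SF-36, using all available week-12 and week-24 values, adjusted for baseline, with patients analysed in the arm to which they were randomised.
- Keep the completer change-score analysis as supportive.

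In section 2.5 or 2.6:
- Distinguish stopping the exercise programme from withdrawing from follow-up.
- State that SF-36 and BDI are collected at weeks 12 and 24, at a routine dialysis visit, whether or not exercise continues.

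The cost is protocol wording, a different SPSS procedure and a few questionnaires. No extra patients are needed, and patients who stop cycling would normally still attend for dialysis (two to three times a week according to the Introduction). There are two downsides. The model assumes data missing at random, so it does not remove loss that depends on unobserved outcomes. The estimated effect may also be smaller, because it includes patients who did not keep up the exercise.

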### 2.6. Safety

The criteria for immediate interruption of the exercise includes intense physical exhaustion, chest pain, dyspnea, dizziness, unstable heartbeat and blood pressure, cramping, or fatigue of the lower limbs. For each participant, serious adverse events and reasons for withdrawal from this study will be recorded accordingly.

## 3. Discussion

Despite good evidence on the benefit of exercise training on physical function, and that such training could reduce a sedentary lifestyle among HD patients, the benefits related to different frequencies of intradialytic exercise protocols in Asian populations is largely unclear. While an intervention with intradialytic exercise is generally considered safe among diverse racial and cultural populations, the best frequency of interventions remains to be investigated.

HD is associated with a high prevalence of psychological problems [27]. Among the HD population, depression is the most common mental disorder. Furthermore, the prevalence of depression in these patients is higher than those in other chronic disease populations [27]. A previous study reported that, based on the mental component scale of SF-36, Taiwanese HD participants had scores significantly lower than the general population [28]. While a recent systematic review advocated that regular exercise may reduce depression and fatigue in HD patients [29], results are still inconsistent across studies [30,31,32]. Hence, our study aims to provide useful information bridging the knowledge gap in Asian populations.

Current evidence supports that moderate-intensity exercise training effectively improves HRQoL [33]. In addition, two systematic reviews and meta-analyses showed that intradialytic exercise is associated with better HRQoL [23,31]. However, another two studies reported no significant difference in HRQoL after intradialytic exercise [29,34]. Regarding the mode of intradialytic exercise, Gomes et al. reported that aerobic exercise alone is not significantly associated with HRQL [32]. In our proposed study on patients under HD, we will incorporate resistance training for knee extensors after the aerobic cycling exercise. Together, they will likely constitute a more comprehensive exercise program.

Systematic reviews and meta-analyses found a significantly improved PCS in the intradialytic exercise group, but not in the MCS [32,35,36]. However, some subdomains of the MCS are still improved after intradialytic exercise. These subdomains include “limitations due to emotional problems” scores in an Iranian study [37], and “bodily pain” scores in a Korean study [38]. As mental problems constitute an important component of life quality, they should not be overlooked in HD patients. Compared with the US general population and US HD cohorts, Taiwanese HD patients have substantially lower physical and mental aspects of life quality [29]. It is well known that for HD patients, their poor physical dimension of HRQoL predicts higher mortality [39]. Therefore, our study will use the SF-36 score as our primary outcome measure, aiming to evaluate the effects of different frequencies of intradialytic exercise on HRQoL.

Blood pressure is regulated through various neural mechanisms involving the sympathetic nervous system, vasoconstriction, and baroreflex activity. During HD, a patient may experience acute hypotension, primarily due to hypovolemia and poor compensatory mechanisms to counter the reduced intravascular volume. In addition, autonomic dysfunction is highly prevalent in these patients, and it has been implicated in the increased risk of blood pressure instability during HD [40,41,42]. In the supine position, SBP is lower due to the reduced effect of gravity on blood in its return to the heart [43]. HD is typically conducted in either a lying or a seated position. While exercise-induced hypotension is of concern for patients and their healthcare givers, our study protocol involves intradialytic exercise in a supine posture, simply to minimize the exercise-induced hypotension.

Most intradialytic exercises in the literature, including the best-known CYCLE-HD study, were conducted for 30 min and given three times a week [11,13,14,15,16]. There is only one study that used the exercise frequency of two times a week, and the training mode involved resistance training and stretching, but not aerobic training [44]. Some other studies also adopted the exercise frequency of two to three times a week, such as those of Vilstreren et al., Chigira et al., and Bae et al. [45,46,47]. To our knowledge, no study has yet directly compared intradialytic exercise groups specifically between three times and two times a week. Since cycle ergometer devices and healthcare givers monitoring intradialytic exercise may be limited in some hospitals in different countries, whether the frequency of intradialytic exercise could be reduced is a crucial and practical issue that needs to be clarified. Hence, we have designed this comparative study in order to clarify this issue and try to fill the knowledge gap in the field of intradialytic exercise.

